## Abstract

**Background:**

Smartphone-based support can reach thousands of smokers and help those who would otherwise try to quit smoking by themselves with little chance of success. Nicotine medications double the chances of quitting smoking, but few smokers use them, and they often use them for too short a time and at an insufficient dose. It is therefore important to increase access to support for smoking cessation and compliance with nicotine therapy. The objectives of this study are to assess whether the Stop-Tabac application (app) is effective for smoking cessation and to examine whether the outcome is influenced by the personal characteristics of participants.

**Methods:**

Trial design: this is a two-arm, parallel-group, superiority, individually randomized, “placebo” controlled trial in 5200 smokers, with follow up after 1 week, 1 month and 6 months. The participants are adult daily smokers (*N* = 5200) enrolled on the Internet, living in France or Switzerland. The intervention is the Stop-tabac fully-automated app for smartphones, which was launched in 2012 and continuously improved thereafter. It includes fact sheets; calculators of cigarettes not smoked, money saved, and years of life gained; an interactive “coach” that provides automated, individually tailored counseling messages based on the user’s personal profile, sent regularly for 6 months; immediate feedback during episodes of craving and tobacco withdrawal symptoms; a discussion forum (“The Tribe”) where participants provide and receive social support; a quiz that informs users in a playful way; and a module on nicotine therapy that includes personalized feedback and follow up. The outcome is self-reported smoking cessation after 6 months (no puff of tobacco in the past 4 weeks), and after 1 week and 1 month (no puff in the past 7 days). Participants will be randomized automatically based on a list of random numbers. Participants, assistants in charge of collecting follow-up data and data analysts will be blinded to allocation. Funding is provided by the Swiss National Science Foundation, CHF 194,942 (EUR 182,200, USD 200,700), grant 32003_179369. [name]’s salary is paid by the University of Geneva, YK’s salary is paid by the Lausanne University Hospitals.

**Discussion:**

There is little evidence from randomized trials of the impact of health apps in general and of smoking cessation apps in particular. This study will fill this gap.

**Trial registration:**

ISRCTN Registry: ISRCTN11318024. Registered on 17 May 2018.

## Background

### Current state of research in the field

Tobacco smoking is the first avoidable cause of death and disease in developed countries [1, 2]. The mass level dissemination of smoking cessation interventions remains one of the most effective and cost-effective ways to decrease smoking prevalence and subsequently mortality from cancer, cardiovascular diseases and lung diseases [3, 4].

When smokers try to quit, 70% of them try by themselves without professional help or medications [5]. Among people who try to quit smoking by themselves, smoking abstinence rates after 12 months are as low as 3–5% [6]. Smokers rarely seek professional support, because of time constraints or the financial cost, or because many healthcare providers do not offer satisfactory smoking cessation support [7]. Few smokers use pharmacotherapy during quit attempts, either because of misconceptions about the nature of addiction and about the benefits and risks of these medications or because of their cost [8]. Many smokers overestimate the risks of nicotine medications, and observance is poor among users [9, 10]. Therefore, increasing the proportion of smokers who try to quit, improving the success rate in those who try, and increasing the use of behavioral support and of nicotine therapy during quit attempts are public health priorities. It is necessary to extend smoking cessation counseling beyond specialized clinics, doctors’ offices, and telephone helplines, in order to reach the thousands of smokers who never receive support from these sources. Mobile phone-based interventions are an optimal tool for this, because they are available 24 h a day/7 days a week/365 days a year, everywhere and often at no charge. A review concluded that, at a global level, text messaging on mobile phones is one of the most affordable effective interventions to assist tobacco cessation [11]. A Cochrane meta-analysis showed that old-fashioned text messaging on mobile phones is effective for smoking cessation (relative risk 1.67), although several of the included studies showed no effect [12]. The authors of this review did not find any randomized trial of modern smartphone apps that fulfilled their inclusion criteria and recommend that more trials should be conducted in this field [12].

#### Smartphone-based smoking cessation support

There is currently a multi-billion-dollar industry in smartphone applications (apps) that disseminate health information on many topics and provide individually tailored support at population level [13–15]. Potentially, smartphone apps could be more effective than text messaging, because the best apps include several features in addition to text messaging (e.g. discussion forums and individually tailored feedback). However, literature reviews conclude that the average quality of apps for smoking cessation is poor, that few apps adhere to guidelines for treating tobacco dependence, that few apps provide individually tailored feedback, and that most apps use only simplistic tools (e.g. calculators of cigarettes not smoked and money saved) [13, 16–18]. One review concludes that in the field of smoking cessation, only 4% of the 50 most commonly downloaded apps have any scientific support, and that only half of the scientifically vetted apps were still available to consumers at the time of the review [17].

There are few published randomized controlled trials (RCT) of smartphone apps for smoking cessation; these trials were conducted in small samples, their results are inconclusive [19–23], and a recent review concludes that good quality trials in large samples are needed [24]. We know of no published randomized trial in a sample large enough to detect a sustained effect of these apps on smoking cessation. The present study will fill this gap in the literature: it includes an adequate control group, sufficiently long follow up (6 months) to fulfill the inclusion criteria in the Cochrane reviews, and it includes a sample large enough to detect a statistically and clinically significant effect.

There is a need for high quality, professionally developed, effective smartphone-based smoking cessation interventions. The Stop-tabac application was developed to fulfill these criteria: its authors are experienced specialists in the field of tobacco dependence, the app is based on theory and on the scientific evidence, and it provides individually tailored advice. The app was iteratively improved over the past 8 years based on feedback received from users [25]. A recent academic review ranked the Stop-Tabac app among the best five smoking cessation apps worldwide [18].

#### Nicotine replacement therapy

Nicotine replacement therapy (NRT) multiplies the chances of quitting smoking by 1.6 compared with placebo [26], and clinical guidelines recommend NRT as a first line treatment for tobacco dependence [27, 28]. However, too few smokers use NRT during quit attempts [5, 29]. Many smokers who use NRT do so without behavioral support, which means that they do not obtain the full benefit this treatment can offer, in particular because of poor compliance: they use too small doses during too short a time [9, 10, 30, 31]. Smokers also have misconceptions about the efficacy and risks of NRT [10]. To address this problem, the Stop-tabac app includes a module aimed at increasing the use of and compliance with NRT.

#### Combining nicotine therapy with smartphone-based behavioral support

Research shows that compliance with NRT increases with the amount of behavioral support received [26], and that behavioral support increases quit rates in people using NRT [32]. However, few NRT users have access to behavioral support. Therefore, there is a need to produce mass-level behavioral support for people who either are prescribed NRT by their doctor but do not receive behavioral support, or who purchase NRT without a medical prescription. Adding smartphone-based support to nicotine therapy represents an opportunity to increase the effectiveness of both components, including by improving compliance with NRT (better dosage and longer treatment duration). Several studies showed that interactive, computer-based behavioral treatments combined with NRT can improve quit rates better than NRT alone [33–35]. Whether smartphone apps can produce the same effect has not been explored.

### In summary, what is not known on this topic

Even though over 400 different smoking cessation apps are available, the quality of most of them is poor [13, 16–18], there are few published randomized trials of smartphone apps for smoking cessation, most of these trials were conducted in very small samples, and their results are inconclusive overall [19, 20, 22, 24]. It is not known whether these apps actually help people stop smoking and maintain abstinence over several months, neither is it known whether these apps elicit quit attempts in current smokers or improve NRT usage. Our study will address these important questions, using a sample size much larger than in previous trials, which will provide sufficient statistical power. Our study includes a control group that uses a “placebo” app, which reinforces the likelihood that any observed association will be causal.

The value of the mobile health industry is projected to be 59 billion USD in 2020 [15]. Health apps are massively used, even though very few of them have ben rigorously evaluated, it is therefore important to evaluate these apps in randomized controlled trials.

## Methods/design

### Objectives

The objective is to test whether the Stop-tabac smartphone application (iOS and Android) improves smoking cessation rates in current smokers and helps them maintain abstinence over 6 months, compared with quit rates observed in a control group, and to measure the size of this effect.

Secondary objectives are:
To study whether the outcome is influenced by the characteristics of participants, such as dependence level, demographics (sex and age), smoking history, and depression.To assess whether the app has any effect on motivation to quit, quit attempts, use of NRT, e-cigarettes and heated tobacco products, number of cigarettes smoked per day, and perceived usefulness of the app.

### (Fig. 1 ) Study design

This is a two-arm, parallel-group, superiority, individually randomized, “placebo” controlled trial with follow up after 1 week, 1 month and 6 months.

**Fig. 1 Fig1:**
[figure not shown]
Flowchart of participants

#### Participants and recruitment

Participants are 5200 smokers who live in Switzerland and in France. The study is advertised on the Internet and social networks, and by smoking prevention organizations. Recruitment is through self-identification and self-selection.

#### Outcomes

##### Primary outcome

The primary outcome is smoking cessation: the proportion of participants at the 6-month follow up who report they have not smoked even a puff of tobacco in the previous 4 weeks.

##### Secondary outcomes

Secondary outcomes are:
Smoking cessation: proportion of participants who report they have not smoked even a puff of tobacco in the previous 7 days, assessed at each follow-up.Smoking cessation as defined in the Russell Standard [36]: proportion of participants at the 6-month follow up who report they smoked ≤5 cigarettes in the past 6 months but did not smoke even a puff of tobacco in the past 7 days, and proportion of participants at the 4-week follow up who report they smoked ≤ 5 cigarettes in the past 4 weeks but did not smoke even a puff of tobacco in the past 7 days.Abstinence from both smoking and vaping: the proportion of participants who report they did not smoke any tobacco or use nicotine-containing e-cigarettes or heated tobacco products after their target quit date, assessed at each follow up.Nicotine use: the proportion of participants who used nicotine therapy, nicotine-containing e-cigarettes or heated tobacco after their target quit date, assessed at each follow up.Perceived usefulness of the app: the question reads: “Did the *Stop-Tabac* app for mobile phones help you quit smoking?”, and is answered on a Likert-type scale with 6 response options ranging from “Yes, enormously” to “On the contrary, it made me smoke or start smoking again”, assessed at each follow up.App use: the proportion of participants who report using any smoking cessation app after their target quit date, assessed at each follow up.

Among those who smoke at follow up:
Intention to quit smoking: the proportion of participants who answer each of the response options to the question: “Do you intend to quit smoking? (response options: I have firmly decided to quit/I consider quitting/No), assessed at each follow up.Quit attempts: the proportion of participants who report they seriously tried to quit smoking after their target quit date (response options: yes/no), assessed at each follow up.Amount smoked: mean number of cigarettes smoked per day, and change since baseline in cigarettes per day (mean change score), assessed at each follow up.

Secondary outcomes from data collected automatically by the app:
Duration of app use (mean number of days between the first and last use of the app) and frequency of app utilization (mean number of times the app was opened), recorded automatically at individual level, assessed at 6-month follow up only.

Inclusion criteria:
Daily cigarette smokerHas been a daily smoker for at least 1 yearAge ≥ 18 yearsSets a target quit date within 1 month of enrollment, and commits to quit on this dateProvides informed consent onlineCommits to complete all follow-up questionnairesCommits to use the appOwns a smartphone (Android or iOS) and has regular access to e-mailProvides a postal address, a telephone number, and a valid e-mail addressLives in Switzerland or in France

The exclusion criterion is prior use of the Stop-tabac app for smartphones (self-report).

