#### Data to be collected

The primary outcome is self-reported smoking abstinence after 6 months (no puff of tobacco in the past 4 weeks). This is the criterion recommended by the American Food and Drug Administration (FDA) to assess outcome in smoking cessation studies [41]. We also assess outcome using the “Russell Standard”, a recently suggested standard for smoking cessation trials: continuous 6-month (at 6 months) or 1-month (at 1 month) abstinence allowing for smoking ≤ 5 cigarettes after the target quit date, but no cigarette in the past 7 days [36].

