#### Potential bias

Participants consist of volunteers and may not be representative of all smokers. We will compare our sample to representative samples of smokers in Switzerland and France. There are no restrictions to obtaining smoking cessation support outside the study. We ask participants whether they used NRT, e-cigarettes, heated tobacco, or smoking cessation apps during the study, and will use this information in our analysis and interpretation of the results.

There is a risk that participants in the more engaging “complete” app (with push notifications) will be more burdened and delete the app or disable the app notifications, but the current content and frequency of reminders have been considered acceptable by app users over the years.

All answers are given via drop-down menus or radio buttons (except names and addresses), and thus only valid answers are recorded. At baseline, participants are required to answer all questions (an incomplete form cannot be sent) and thus there are no missing data. At follow up, answers to the questions on smoking status (any smoking in the past 7 days, 4 weeks, and 6 months) are required, but participants can send an incomplete form as long as they answer these questions. An assistant will enter the data for questionnaires on paper (collected by post or over the phone) by single data entry.

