#### Intention to treat, missing data

For the primary outcome, participants will be evaluated in an intention-to-treat analysis, with the baseline number of participants as the denominator. Participants absent at follow-up will be counted as smokers, except those who are dead. We will conduct sensitivity analyses with different assumptions for missing data. For each follow-up questionnaire, non-responders will be counted as smokers for this specific questionnaire. A participant who is missing at the 1-month follow up but then returns as a non-smoker for the 6-month follow up will be counted as smoker for the 1-month follow up only.

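### The 6-month Russell Standard outcome is scored from the 6-month report alone, so a participant whose own 1-month report exceeds the 5-cigarette allowance can still count as continuously abstinent

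*Protocol article*

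**What the plan says.** All places are in the protocol article.

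- **Secondary outcomes** defines the 6-month Russell Standard outcome by two answers given at 6 months. The first concerns the amount smoked: the "proportion of participants at the 6-month follow up who report they smoked ≤5 cigarettes in the past 6 months". The second is a condition on the final week, namely no tobacco at all in the last 7 days.
- The same section defines the 1-month version from the 1-month survey: the "proportion of participants at the 4-week follow up who report they smoked ≤ 5 cigarettes in the past 4 weeks", again with no smoking in the last 7 days.
- **Data to be collected** says what the outcome stands for: "continuous 6-month (at 6 months) or 1-month (at 1 month) abstinence allowing for smoking ≤ 5 cigarettes after the target quit date".
- Other smoking reports are also collected at each survey. One is the proportion who "have not smoked even a puff of tobacco in the previous 7 days, assessed at each follow-up". Another, among those still smoking, is the "mean number of cigarettes smoked per day, and change since baseline in cigarettes per day (mean change score), assessed at each follow up".
- **Potential bias** says that "answers to the questions on smoking status (any smoking in the past 7 days, 4 weeks, and 6 months) are required" on any submitted follow-up form.
- **Intention to treat, missing data** says: "For each follow-up questionnaire, non-responders will be counted as smokers for this specific questionnaire". Its example is a person absent at 1 month who returns at 6 months. The section has no rule for a person who answered at 1 month and reported smoking.

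**The concern.** The definition and the stated construct do not match. The construct is abstinence since the target quit date with at most 5 cigarettes. The scoring rule is a single recall, made about five months after the 1-month survey, of how much was smoked over half a year. The trial will hold a nearer report for the first month, on the same 5-cigarette threshold, and the rule does not consult it.

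One participant could then appear in the results with two incompatible statuses: over the allowance at 1 month, and within it for a 6-month period that contains that month. The likely candidates are late or repeat quitters, who smoked through the first weeks, stopped later and remember the early period too kindly.

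The objectives include helping smokers stay abstinent over 6 months. The Russell Standard outcome is the tobacco-smoking measure that addresses this while tolerating a few slips. With no biochemical verification, agreement with the participant's own earlier report is one of the few checks available.

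**Working it through.** **1. Is there a real contradiction?** Surveys are sent 1 week, 1 month and 6 months after the target quit date. A month is at least 28 days, so the 4-week window of the 1-month survey lies wholly after that date. More than 5 cigarettes in that window is therefore more than 5 since the quit date, and the person does not meet the construct in Data to be collected. The definition in Secondary outcomes still counts that person if the 6-month answers are favourable.

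| 1-month report | 6-month report | Scored at 6 months as written | Meets the stated construct? |
|---|---|---|---|
| 5 or fewer in 4 weeks | 5 or fewer in 6 months, none in 7 days | abstinent | nothing contradicts it |
| more than 5 in 4 weeks | more than 5 in 6 months | not abstinent | no |
| more than 5 in 4 weeks | 5 or fewer in 6 months, none in 7 days | **abstinent** | **no** |
| some smoking in last 7 days, total 5 or fewer | 5 or fewer in 6 months, none in 7 days | abstinent | nothing contradicts it |
| survey not answered | 5 or fewer in 6 months, none in 7 days | abstinent | cannot be checked |

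Only the third row is misclassified.

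**2. The plan's own figure.** The plan gives no rate or power for this outcome. Its sample size is for the primary outcome: 12.5% against 10%, 2,600 per arm, 80% power, 95% confidence (read as two-sided 5%). Power is Φ{[|p2 − p1| − 1.96·√(2p̄(1 − p̄)/n)] / √[(p1(1 − p1) + p2(1 − p2))/n]}.

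With p1 = 0.10, p2 = 0.125, p̄ = 0.1125 and n = 2,600, this is Φ[(0.0250 − 0.0172)/0.00876] = 0.81. The required size is 2,507 per arm without continuity correction and 2,586 with it, so the stated 2,600 is consistent. Nothing in this point changes it.

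**3. Illustration of dilution.** None of these inputs is in the documents. Assume true continuous abstinence of 5% (control) and 6.5% (app). Assume a further 6% in each arm who quit late or again and are abstinent at 6 months, and that a share m of them wrongly report 5 or fewer cigarettes. The observed rate is the true rate + m × 6%, and the number wrongly counted per arm is 2,600 × 0.06 × m.

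| m | Wrongly counted per arm | Control | App | Difference | Risk ratio | Power |
|---|---|---|---|---|---|---|
| 0 | 0 | 5.0% | 6.5% | 1.5 points | 1.30 | 0.64 |
| 0.05 | 8 | 5.3% | 6.8% | 1.5 points | 1.28 | 0.62 |
| 0.30 | 47 | 6.8% | 8.3% | 1.5 points | 1.22 | 0.53 |

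**4. The pattern matters.** Suppose instead that the contradicted people are the same share f of counted abstainers in each arm, and borrow 10% and 12.5% as the counted rates. With f = 10%, removing them gives 10% × 0.9 = 9.0% and 12.5% × 0.9 = 11.25%. About 26 and 32 people are reclassified, the risk ratio stays at 1.25 and power goes from 0.81 to 0.77. Here the check corrects the level but does not sharpen the comparison. Dilution is thus a consequence of the assumptions in step 3, not of the documents.

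**The case against.** The strongest reply is that this is silence rather than error: the article is condensed, and rules for conflicting answers across surveys are often left to an analysis plan. In part this stands. No sentence says that earlier reports are to be disregarded, and a plan not shown could add a check. But the article does not merely leave scoring open. It gives an explicit rule that, followed as written, puts the third row of the table in the wrong class.

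Several stronger readings are tempting and are not supported.

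- **Any earlier report of smoking disproves continuous abstinence.** It does not, because up to 5 cigarettes are allowed.
- **The missing-data section orders each survey to be scored in isolation.** Its sentence and its example concern non-responders only.
- **The daily amount at 1 week or 1 month shows who exceeded 5.** Turning it into a total needs the number of days smoked, which is not listed as collected. The daily amount is also not among the items named as compulsory.
- **Sustained abstinence rests on this outcome alone.** Secondary outcomes also lists abstinence from tobacco, nicotine e-cigarettes and heated tobacco since the quit date.
- **The comparison is biased towards the app.** Nothing in the documents indicates that false recall differs by arm.

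It is also fair to object that a check based on the 1-month survey can reclassify only those who answered it. If early response differs by arm, the check could itself introduce a difference. That stands, and it is why both versions should be reported.

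**Conclusion.** The point holds in a limited form. The 6-month Russell Standard outcome, as defined, can count as continuously abstinent a participant whose own 1-month report exceeds the 5-cigarette allowance, contrary to the construct the article names. That conclusion rests on the wording alone.

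Its size is unknown. The illustration ranges from negligible (risk ratio 1.30 to 1.28) to moderate (1.30 to 1.22), but the upper end needs nearly one in three late quitters to answer wrongly. It also shows all false reports, which is more than the 1-month check could catch.

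A reader might infer that the trial's main result or its sample size is in doubt. It is not: the primary outcome asks only about the 4 weeks before the 6-month survey, and the stated power refers to that outcome. This is a desirable improvement to one secondary outcome.

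**What to change.** Add one condition to the 6-month Russell Standard outcome: a participant counts as abstinent only if the 1-month survey, where answered, does not report more than 5 cigarettes in the past 4 weeks. State that:

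- an unanswered 1-month survey is not a contradiction, and neither is a blank on that item;
- smoking in the last 7 days, reported at 1 week or 1 month, is not a contradiction by itself;
- the number reclassified and the 1-month response rate are reported for each arm;
- the version based on 6-month recall alone is shown beside it.

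The cost is a few lines of analysis code on data the trial already plans to collect. The abstinence rate will be slightly lower. Only those who answered at 1 month can be reclassified, so unequal early response between arms could matter; the response rates and the paired results let the reader judge that.

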Brief texts on tobacco dependence, tobacco withdrawal symptoms, tobacco dependence treatments, relapse situations, mood management, risks of smoking and benefits of quitting, e-cigarettes, and heated tobacco products.Calculators (number of cigarettes not smoked, money saved since quitting, additional days of life expectancy gained since quitting).Immediate feedback when participants experience challenging situations (e.g. relapse situations, craving episodes).A quiz (42 questions), which allows the transmission of knowledge in a playful way.A link that automatically dials the phone number of the national quit-lines in France or Switzerland.The “Coach”, an automatic system that produces individually tailored feedback messages and sends periodic reminders (push notifications within the app). Each participant receives individually tailored advice and follow-up messages based on their target quit date, level of tobacco dependence, perceived advantages and drawbacks of smoking, and motivation to quit. The duration of this automated intervention is 6 months. Participants can disable the push notifications.A discussion forum, “The Tribe”, permanently (24 h a day/7 days a week/365 days a year) moderated by a psychologist helped by volunteers under her supervision. An influential guideline identified social support as an important and effective component of smoking cessation interventions [27]. The “Tribe” is quite active and is very appreciated by users.A module on nicotine replacement therapy (NRT) that includes fact sheets (NRT utilization, benefits and side effects, where and how users can obtain NRT); frequently asked questions (FAQ); and a series of brief individually tailored feedback messages, based on users’ responses to questions on current NRT use, knowledge about NRT, intention to use NRT, craving and withdrawal symptoms. If users report withdrawal symptoms and if they have quit smoking for < 3 months, they receive automated messages telling them to use NRT. These messages insist on the importance of using a sufficient dose of nicotine and not interrupting the treatment prematurely.A module on electronic cigarettes that includes a series of brief individually tailored feedback messages, based on users’ responses to questions on current vaping, intention to use e-cigarettes, opinions about the effects of vaping on smoking cessation and nicotine withdrawal symptoms, perceived side-effects, and perceived addictiveness of e-cigarettes.

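### The *Nicotine use* secondary outcome pools NRT, e-cigarettes and heated tobacco, so a difference between arms cannot be attributed to any one product and the objective on product use is not answered as written

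*Protocol article*

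**What the plan says.** Objectives lists as a secondary aim: "To assess whether the app has any effect on motivation to quit, quit attempts, use of NRT, e-cigarettes and heated tobacco products". The products are named one by one, with no direction and no ranking among them.

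Two background sections go further on NRT. Under Nicotine replacement therapy, "the Stop-tabac app includes a module aimed at increasing the use of and compliance with NRT". The summary of what is not known says of existing apps: "neither is it known whether these apps elicit quit attempts in current smokers or improve NRT usage", and adds that this study will address such questions.

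Secondary outcomes defines *Nicotine use* as "the proportion of participants who used nicotine therapy, nicotine-containing e-cigarettes or heated tobacco after their target quit date", assessed at each follow-up. The other outcome that involves these products is abstinence from smoking and vaping, for participants who "did not smoke any tobacco or use nicotine-containing e-cigarettes or heated tobacco products after their target quit date". It leaves NRT out.

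On data collection, Potential bias says: "We ask participants whether they used NRT, e-cigarettes, heated tobacco, or smoking cessation apps during the study". It assigns the answers to analysis and interpretation in general, not to a comparison of each product by arm.

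**The concern.** The objective concerns three products, and the outcome gives one number. The three are joined by *or*, so a participant counts once whichever product was used. A medication that the app sets out to promote is counted in the same way as a heated tobacco product. If the composite rises in the app arm, the reader cannot tell whether NRT use rose. If it does not move, the reader cannot tell whether NRT use stayed still.

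At stake is a secondary question on which the protocol lays weight. NRT use is presented as a route by which the app should work, yet the listed outcomes would allow a rise in vaping or heated tobacco to be read as success on NRT.

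**Working it through.** **1. The plan's own figure.** The document gives no figure for product use. Its only power statement is for the primary outcome: 12.5% vs 10%, 2 × 2600, 80% power, 95% confidence. The normal-approximation formula is

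power = Φ{ [ |p1 − p0| − 1.96·√(2p̄(1−p̄)/n) ] / √( [p1(1−p1) + p0(1−p0)]/n ) }.

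With p1 = 0.125, p0 = 0.10, p̄ = 0.1125 and n = 2600, this is Φ[(0.0250 − 0.0172)/0.00876], or 81.4%. The required size is 2507 per arm without continuity correction and 2586 (5172 in total) with it. The stated 5200 is reproduced and is not in question; 2600 per arm is used below.

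**2. Attribution (any rates).** Suppose, for simplicity, that nobody uses two products, and that control use is NRT 30%, e-cigarettes 25% and heated tobacco 3%. These rates are assumptions. The control composite is 0.30 + 0.25 + 0.03 = 58%. A composite of 63% in the app arm could then come from any of these:

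- NRT up 5 points: 0.35 + 0.25 + 0.03 = 63%
- e-cigarettes up 5 points: 0.30 + 0.30 + 0.03 = 63%
- heated tobacco up 5 points: 0.30 + 0.25 + 0.08 = 63%

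The outcome does not distinguish the three, and no choice of rates changes that.

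**3. Masking (assumed rates only).** NRT rises from 30% to 35%, heated tobacco is 3% in both arms, and e-cigarette use in the app arm varies from a control value of 25%. The setting is n = 2600 per arm, two-sided 5%, full response. With no overlap, the composite is the sum of the three. With independent use, it is 1 − (1−NRT)(1−e-cig)(1−heated); for controls, 1 − 0.70 × 0.75 × 0.97 = 49.1%.

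| E-cigarettes in app arm | Composite, no overlap | Power | Composite, independent use | Power | NRT alone, power |
|---|---|---|---|---|---|
| 25% (unchanged) | 58.0% vs 63.0% | 96% | 49.1% vs 52.7% | 75% | 97% |
| 22% | 58.0% vs 60.0% | 31% | 49.1% vs 50.8% | 24% | 97% |
| 20% | 58.0% vs 58.0% | none (no difference) | 49.1% vs 49.6% | about 5% | 97% |

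The first row has no opposite shift. The other two do, by choice of input. Product items left blank would put real power below all these values.

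**4. Could another outcome fill the gap?** The smoking-and-vaping outcome combines smoking, e-cigarettes and heated tobacco and omits NRT. The models in Statistical analyses and data management relate outcome to cessation tools obtained outside the study. That treats product use as an explanatory variable for quitting and does not compare product use by arm. Elsewhere in the same outcome list, intention to quit is to be reported for every response option, so the authors separate categories explicitly when they mean to.

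**The case against.** The best defence is that a journal article compresses. The one-line outcome may simply list products to be tabulated, Potential bias shows that participants are asked about them, and component reporting is commonly left to an analysis plan that is not shown here. In part this stands: a composite of any nicotine use is a legitimate measure, and if the questions are separate by product, no information is lost. But the article does not leave the definition open. It fixes a single proportion, and that proportion does not match its own objective.

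Two stronger readings are tempting, and the document does not support them.

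- A reader might infer that shifts in opposite directions will cancel, so that a real NRT effect disappears. The document gives no usage rates and predicts no fall in vaping. The app contains "A module on electronic cigarettes that includes a series of brief individually tailored feedback messages", but nothing says that this module reduces e-cigarette use. The last row of the table is a constructed extreme.
- A reader might infer that the secondary objective asks whether the app raises NRT use above all. Objectives asks about any effect on three product classes. Only the two background sections single out NRT, so ranking NRT first would be the reviewer's choice.

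It is also fair to say that Baseline data, which names the products, covers baseline only. The support for product-level answers at follow-up is the sentence in Potential bias alone.

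**Conclusion.** The point holds in a narrow form. As worded, *Nicotine use* is one pooled proportion, no other listed outcome isolates NRT, and a difference between arms cannot be assigned to a product. It therefore answers neither the objective on product use nor the background question about NRT. This rests on the wording alone and needs no assumed rate.

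Masking is a possibility, not an expected result. With e-cigarette and heated tobacco use unchanged, an assumed 5-point NRT rise leaves the composite about 75% (independent use) to 96% power (no overlap). It falls towards nothing only if vaping drops by a similar amount. These figures assume the product rates, 2600 per arm and full response.

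The weight is that of a secondary outcome: worth correcting because it is cheap, with no bearing on the primary analysis, the randomisation or the sample size.

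**What to change.** Before unblinding, replace the single *Nicotine use* outcome with three proportions: use of NRT, of nicotine-containing e-cigarettes and of heated tobacco after the target quit date. Compare each by arm at each follow-up, using the product questions described in Potential bias. Keep the pooled proportion as an additional outcome. Confirm first that the follow-up questionnaire records the products separately.

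State how non-responders and blank product items are counted. The rule in Intention to treat, missing data assigns smoking status only. Potential bias lets a participant return a follow-up form with just the smoking questions answered, so product items can be missing even among responders.

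The timing is workable: Blinding keeps the data blinded until the main analysis is finished, and the section on protocol modifications gives the registry record as the route for a change. Separate proportions chosen after unblinding would be post hoc.

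The cost is revised wording, a few more table rows and a few more secondary comparisons. The split covers use of NRT; it does not measure compliance, the other half of the NRT module's aim.
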